## Abstract

**Background:**

Stable coronary artery disease (CAD), recently termed chronic coronary syndrome (CCS), is a highly prevalent disease. Current treatment strategies often include a relevant placebo effect. The hypothesis is that visual angiographic demonstration of the coronary arteries before and after successful percutaneous coronary intervention (PCI) by itself reduces the symptom burden of stable CAD/CCS.

**Design and methods:**

The PLA-pCi-EBO-pilot-trial is a prospective, multi-center, randomized, controlled investigator-initiated pilot trial to study the effect of visual demonstration of successful PCI on quality of life (QoL) and angina pectoris (AP) in patients with symptomatic stable CAD/CCS. All patients with stable CAD/CCS and successful PCI will be screened. One hundred forty four patients with a frequency of AP ≥ 2/week will be randomized 1:1 stratified for AP frequency > 1/day. The control group will receive the common written procedural report on the procedure. Patients in the intervention group will additionally be given a printout picture of their coronary angiogram both before and after PCI. Primary endpoints are change in the Seattle Angina Questionnaire (SAQ)-derived QoL score 1 and 6 months after PCI. Secondary endpoints are changes in other SAQ-derived scores and dyspnea (NYHA score) 1 and 6 months after PCI.

**Discussion:**

The PLA-pCi-EBO-pilot-trial evaluates the effect of visual angiographic result demonstration on disease symptoms and QoL in patients with stable CAD/CCS on top of PCI. A positive outcome of our study would encourage the routine use of angiographic picture demonstration and has thus the potential to change daily routine in the catheterization laboratory.

**Trial registration:**

German Clinical Trials Register DRKS00017524. Registered on 5 July 2019

## Administrative information

The order of the items has been modified to group similar items (see http://www.equator-network.org/reporting-guidelines/spirit-2013-statement-defining-standard-protocol-items-for-clinical-trials/).

## Introduction

### Background and rationale {6a}

Among patients between 40 and 79 years of age, almost 10% are affected by coronary artery disease (CAD), and the prevalence is rising with growing age [1]. CAD significantly reduces life expectancy by promoting cardiac infarction and development of ischemic heart disease [2]. Patients are often suffering from symptoms such as angina pectoris (AP) and dyspnea, potentially resulting in dramatically reduced quality of life (QoL). Medical and interventional treatment aims to restore optimal coronary blood flow, modify cardiovascular risk factors, reduce cardiac remodeling, treat possible heart failure, and implement secondary prevention. To highlight the chronic nature and dynamic processes of CAD, the latest update of the ESC guidelines changed the term stable CAD to chronic coronary syndrome (CCS) [2, 3]. This term rightly represents an altered and more accurate concept of CAD. For the purpose of avoiding confusion, especially since almost all studies cited in this article have been conducted using the previous nomenclature, we deliberately simplify the differences between the two terms and use stable CAD and CCS as synonyms.

Despite optimal interventional and medical treatment, the symptoms of CAD are often poorly controlled. The COURAGE and FAME2 trials found that appr. 20–30% of patients still suffered from persistent AP and dyspnea on exertion after 1 year of optimal treatment [4, 5]. It is striking that in studies examining antianginal therapies, a large symptom relief in the placebo group can be observed. This is evident, for example, in studies evaluating ranolazine [6] or ivabradine [7] which reported a reduction of the AP frequency of up to 40% in the placebo study arm. The ORBITA trial was published as a seminal work investigating the effects of PCI in patients with stable angina in a randomized, sham-controlled fashion. However, there was no overall difference between groups for exercise capacity testing, angina, or quality of life [8]. Taken together, these results indicate that a relevant part of the symptomatic improvement after medical or interventional treatment might be attributed to the placebo effect and context factors. To further enhance the efficacy of interventions, profound knowledge and understanding of context factors are essential.

The concept of placebo medicine is complex and no clear definition exists [9]. Generally speaking, placebo constitutes the substitution of the active ingredient of a therapeutic intervention through an inactive ingredient in a manner that is indistinguishable for the recipient. Even for a drug with a known mechanism of action, the drug’s pharmacological effect cannot be separated from the psychological effects of its administration and the accompanying physiological consequences [10]. Growing evidence exists for possible mechanisms of the placebo effect. Placebo interventions activate the endogenous opioid system [for review see [11]] and the dopaminergic reward circuit which is crucial for reinforcement, learning, and decision-making [for review see [11]]. Placebos also affect the autonomous nervous system for instance by altering the duration of gastric contractions [10]. The placebo effect is strongly influenced by patients’ expectations [12], learning [12], emotions [13], and personality traits such as optimism [14], empathy [12], and reward responsiveness [14].

Communication forms an essential part of the patient-doctor relationship and is key to ensure patients’ understanding of their disease and treatment and thus propagate therapy adherence. Improved communication is an important context factor often implicated as a huge contributor to the placebo effect [15]. Visualization is a good and effective means to facilitate communication and risk evaluation between patients and the physician. The VIPVIZA trial highlights the importance of the visualization of diagnostic findings to the patient [16].

### Objectives {7}

Given the still limited treatment options for stable CAD and the often significantly reduced quality of life, we hypothesized that the visualization of the severe coronary stenosis before and the angiographic result after successful coronary stent implantation will reduce angina pectoris and thereby improve quality of life.

### Trial design {8}

The PLA-pCi-EBO-pilot-trial is a prospective, multi-center, randomized, controlled investigator-initiated pilot trial to study the effect of visual demonstration of successful coronary intervention on quality of life and angina pectoris in patients with symptomatic stable coronary artery disease. The trial has been approved by the Ethical Committee of the University of Regensburg (19-1261-101). The German Clinical Trials Register registration number is DRKS00017524.

## Methods: participants, interventions, and outcomes

### Study setting {9}

Patients will be recruited in Germany from different clinical settings including a university hospital, a community hospital, and a cardiological clinic.

### Eligibility criteria {10}

Patients with clinical symptoms of stable coronary artery disease such as typical pain, chest discomfort (e.g., pressure, tightness, squeezing, burning), or atypical angina together with dyspnea undergoing cardiac catheterization and stent implantation will be screened for inclusion into the study. The decision for PCI and the choice of implemented technique, stents, balloons, etc. is made by the treating cardiologist based on current guidelines [2] and best clinical practice.

Inclusion criteria are:
Females or males age ≥ 18 yearsSymptomatic CADCCS score for angina pectoris ≥ 2Angina pectoris frequency ≥ 2/weekImplantation of ≥ 1 coronary artery stentGerman speakingSigned informed consent

Abbreviations: CAD, coronary artery disease; CCS, Canadian Cardiovascular Society

Exclusion criteria are:
Cardiac EF ≤ 35%Severe pulmonary diseaseImpaired visionImpaired hearingDementiaTreatment with opioidsHigh-grade cardiac valvular diseaseHb ≤ 7 mg/dLParticipation in another trial of an investigational drug or device

Abbreviations: EF, ejection fraction; Hb, hemoglobin

### Who will take informed consent? {26a}

Written informed consent will be taken after a trained participating consultant has explained the study’s aims, conduct, and procedures to the patients and answered possible questions.

### Additional consent provisions for collection and use of participant data and biological specimens {26b}

The study does not include ancillary studies or the collection of biological specimens.

### Interventions

#### Explanation for the choice of comparators {6b}

Our approach of influencing AP frequency by the simple means of visual demonstration of the angiographic result of PCI is very pragmatic. As no clear recommendation exists, current practice is that some interventionalists demonstrate the interventional result to the patient during the PCI procedure. This will be noted but does not constitute an exclusion criterion because the aim of this study is to compare the explicit visual demonstration of successful PCI to the current clinical practice. The patients in the control group receive only the usual doctor’s note at hospital discharge without any pictorial representation of the treated stenosis.

#### Intervention description {11a}

The patients in the control arm will only receive the written report on the procedure as is current common clinical practice. Patients in the intervention arm will be additionally given a printout of their coronary status (picture angiogram) both before and after PCI to emphasize the outcome of the successful therapy (see Fig. 1). The prints and coronary intervention will be briefly explained to the patient by a qualified physician.

**Fig. 1 Fig1:**
[figure not shown]
Anonymized patient printout of the successful PCI. On the left a coronary angiography of the stenosis is shown and on the right after successful coronary intervention. For better understanding, the stenosis is highlighted by a white circle

#### Criteria for discontinuing or modifying allocated interventions {11b}

As the intervention consists of demonstrating a picture of the angiogram to the patients after successful PCI, there are no serious adverse reactions caused by the intervention to be expected.

#### Strategies to improve adherence to interventions {11c}

The follow-up interviews include the question, if and how often patients in the intervention group have looked at the angiogram picture after hospital discharge. This constitutes necessary information to estimate the relevance and meaning of the picture for the patients. The patients are not encouraged to look at the picture either at the baseline visit or the follow-ups in order to protect this information from being influenced by the investigators’ behavior.

#### Relevant concomitant care permitted or prohibited during the trial {11d}

Routine practice, medication, and clinical check-ups after PCI or possible participation in cardiac rehabilitation programs are not affected by the study protocol.

#### Provisions for post-trial care {30}

Given the harmless nature and singularity of the intervention, no post-trial care is planned. Patients that have been randomized to the control group can request a printout of their angiogram after completion of the study.

### Outcomes {12}

Symptoms such as AP according to the Canadian Cardiovascular Society score and dyspnea according to the NYHA scale will be assessed. The German version of the revised Life Orientation Test (LOT-R) [17] and the German version of the Seattle Angina Questionnaire (SAQ, CV outcomes Inc.) [18] will be filled out by the patient before randomization.

The primary endpoints are:
Change from baseline in the SAQ-derived quality of life score 1 and 6 months after PCI

The secondary endpoints are:
Change from baseline in the other SAQ-derived scores (physical limitation, angina stability, angina frequency, treatment satisfaction, disease perception)Change from baseline in the total SAQ score 1 and 6 months after PCIChange from baseline in dyspnea (NYHA score) 1 and 6 months after PCI

#### Participant timeline {13}

Patients with clinical symptoms of stable CAD such as typical pain, chest discomfort (e.g., pressure, tightness, squeezing, burning), or atypical angina together with dyspnea undergoing cardiac catheterization and stent implantation will be screened for inclusion into the study. One hundred thirty-four patients who fulfill the inclusion and exclusion criteria will be randomized stratified by angina frequency (daily vs not daily) in a 1:1 ratio to receive either only the standard written report or an additional printout of the images acquired during catheterization of both the severe coronary stenosis before and after stent implantation. Baseline scores of dyspnea (NYHA score) and SAQ are measured during the initial hospital visit. After 4 weeks and 6 months, the SAQ will be repeated and the NYHA score reassessed in a telephone interview (see Figs. 2 and 3).

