#### Sample size {14}

The study is designed and powered as a pilot trial to allow for precise parameter estimation for a subsequent confirmatory study. There is sparse comparable data to calculate effect size estimations for the kind of intervention employed in our study. However, clinical observation suggests that our pragmatic approach of influencing AP frequency by the simple means of visual demonstration of the angiographic result of PCI has a strong effect on the patients. The ISCHEMIA trial revealed relevant symptomatic improvement in patients with more severe AP [19]. Placebo- and sham-controlled trials have shown that large parts of the treatment effect of conservative and interventional therapeutic strategies for AP can be ascribed to context factors such as the one employed in this pilot study. Thus, we think it is reasonable and realistic to expect a difference of 10 points with a standard deviation of 20 between the control and interventional groups regarding the quality of life scale of the SAQ (effect size of *d* = 0.5 (medium effect)). This difference would also be highly clinically relevant. To show an effect size of *d* = 0.5 with a power of 80% (*β* = 0.2) at a two-tailed significance level of *α* = 0.05, *n* = 64 patients need to be included in each group. With an estimated drop-out rate of 10%, a total of *n*_total_ = 144 patients need to be recruited.

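### The number to be randomised is 134 in the participant timeline but 144 in the abstract and sample size section; at 134 with the planned 10% drop-out, the stated 80% power is not reached.

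*Protocol article*

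**What the plan says.** The participant timeline (item 13) reads: "One hundred thirty-four patients who fulfill the inclusion and exclusion criteria will be randomized". It goes on to describe a 1:1 allocation stratified by daily versus non-daily angina.

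The abstract, under design and methods, describes the same allocation with another number: "One hundred forty four patients with a frequency of AP ≥ 2/week will be randomized 1:1".

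The sample size section (item 14) gives the derivation. The investigators "expect a difference of 10 points with a standard deviation of 20 between the control and interventional groups", an effect size of 0.5. They ask for 80% power "at a two-tailed significance level of *α* = 0.05" and arrive at 64 patients in each group. The section then allows for loss: "With an estimated drop-out rate of 10%, a total of" 144 is required.

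The statistical methods section (item 20a) excludes patients with a missing endpoint from the analysis of that endpoint. Drop-outs therefore reduce the number analysed.

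**The concern.** The abstract and the timeline both state how many patients will be randomised, in the same 1:1 stratified scheme. The two figures cannot be read as screened versus randomised, or as randomised versus evaluable. Each is spelled out in words, so a misread digit is an unlikely cause. The timeline gives no reason for the lower number.

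The number to be randomised determines when enrolment is complete, how long the allocation list must be, and the total against which completeness of the trial is judged. The trial status section reports that recruitment is still running. With two published targets, enrolment could end at either and be called complete. If it ended at 134 with the drop-out the article itself expects, the analysed sample would fall below the 128 on which the power statement rests.

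**Working it through.** **Inputs** (sample size section unless noted): difference 10 points; SD 20; d = 10/20 = 0.5; two-sided α = 0.05; power 80%; drop-out 10%; allocation 1:1 (sequence generation, item 16a); patients with a missing endpoint excluded (item 20a).

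**Step 1: reproduce the stated group size.** Solving the two-sample t-test for power 0.80 gives n = 63.77, so 64 per group, as stated. The normal approximation gives n = 2 × (1.960 + 0.842)² × (20/10)² = 62.8, so 63 per group. The stated 64 is the t-test figure, and 2 × 64 = 128 evaluable patients are needed.

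**Step 2: reproduce the stated total.** With drop-out as n/(1 − 0.10): 64/0.9 = 71.1, so 72 per group and 2 × 72 = 144. This matches the stated total. Inflating the total instead gives 128/0.9 = 142.2, so 143.

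**Step 3: look for a route to 134.** The evaluable number is 128. Multiplying by 1.10 instead of dividing by 0.90 gives 128 × 1.1 = 140.8, so 141. Neither is 134. A 5% allowance comes close (128 × 1.05 = 134.4), but the article states 10% and no other rate.

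**Step 4: consequence of each target under the stated 10% loss.**

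| Randomised | Evaluable | Per group | Power, t-test | Power, normal approximation |
|---|---|---|---|---|
| 134 | 134 × 0.9 = 120.6 | 60.3 | 77.7% | 78.4% |
| 144 | 144 × 0.9 = 129.6 | 64.8 | 80.6% | 81.2% |

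Rounded down to 60 per group, the t-test power at 134 is 77.5%.

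**Step 5: how much loss 134 can absorb.** 1 − 128/134 = 4.5%. A target of 134 keeps 128 evaluable patients only if drop-out is at most 4.5%, less than half the planned rate. With no drop-out at all (67 per group), power would be 81.9%.

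**The case against.** The strongest reply is that 134 is an isolated slip in a descriptive section. The target is set in the sample size section with a full derivation and repeated in the abstract. The trial status section measures progress against the calculated sample size, and the only calculated total is 144. The allocation list is not said to be built on 134. If 144 is the working figure, no power is lost. This is probably the right reading, and it means that nothing in the article shows 134 to be the number at which randomisation will in fact stop. It does not remove the contradiction: a reader still has to decide which of two plain statements about randomisation to believe.

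The second reply is that the loss would be small even if 134 were real: 2.3 points below 80% by t-test at 60.3 per group, and 1.6 points by the normal approximation. That is correct.

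Third, the planned ANCOVA could recover the gap if the SD of 20 is unadjusted. With 60.3 per group, an assumed covariate correlation of 0.2 gives about 79% power, 0.3 about 81% and 0.5 about 88%. The article gives no such correlation, and its calculation takes no credit for one, so this remains an assumption.

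Fourth, this is a pilot meant to estimate parameters for a later trial. The 95% confidence interval half-width, t × 20 × √(2/n), is about 7.2 points at 60.3 per group and about 7.0 at 64.8, so precision hardly changes. Even so, the article commits to a formal power of 80%, and that statement should agree with the number randomised. These replies bear on how serious the error is, not on whether it is one.

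**Conclusion.** The concern holds. The article states both 134 and 144 as the number to be randomised, and only 144 follows from its own inputs. The gap is 10 patients, or 10/144 = 6.9% of the derived target. At 134 with 10% drop-out, about 60 per group are evaluable instead of 64, and power is 77.5% to 77.7% instead of 80%; 144 gives 80.6%.

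These power figures assume an unadjusted two-sample t-test, the stated d of 0.5, and complete loss of drop-outs from the analysis. The contradiction is the main finding. The power loss, about 2 points, is a modest consequence that depends on 134 being used.

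**What to change.** Correct the participant timeline to 144, the figure in the abstract and the sample size section. Confirm that the allocation list, the sealed envelopes and the registry entry carry the same number.

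If 134 is the intended target, change the abstract and the sample size section instead: about 60 evaluable per group and about 77.5% power at 10% drop-out, or a justified lower drop-out rate (at most 4.5% to keep 128 evaluable). Under item 25 of the article, a change of sample size needs a formal amendment and ethics approval, so that route would have to be documented.

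The first option costs a one-word correction and a short check of the trial's own records.

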**Fig. 2 Fig2:**
[figure not shown]
Participant timeline

**Fig. 3 Fig3:**
[figure not shown]
SPIRIT figure

#### Sample size {14}

The study is designed and powered as a pilot trial to allow for precise parameter estimation for a subsequent confirmatory study. There is sparse comparable data to calculate effect size estimations for the kind of intervention employed in our study. However, clinical observation suggests that our pragmatic approach of influencing AP frequency by the simple means of visual demonstration of the angiographic result of PCI has a strong effect on the patients. The ISCHEMIA trial revealed relevant symptomatic improvement in patients with more severe AP [19]. Placebo- and sham-controlled trials have shown that large parts of the treatment effect of conservative and interventional therapeutic strategies for AP can be ascribed to context factors such as the one employed in this pilot study. Thus, we think it is reasonable and realistic to expect a difference of 10 points with a standard deviation of 20 between the control and interventional groups regarding the quality of life scale of the SAQ (effect size of *d* = 0.5 (medium effect)). This difference would also be highly clinically relevant. To show an effect size of *d* = 0.5 with a power of 80% (*β* = 0.2) at a two-tailed significance level of *α* = 0.05, *n* = 64 patients need to be included in each group. With an estimated drop-out rate of 10%, a total of *n*_total_ = 144 patients need to be recruited.

#### Recruitment {15}

More than 2000 PCIs are performed at the study centers each year. Patient lists are screened at the end of each day for probable participants (i.e., successful PCI and chronic coronary syndrome) and eligibility criteria are checked. It is estimated that approximately 200 (i.e., 10% of the total) of the patients present with chronic coronary syndrome.

### Assignment of interventions: allocation

#### Sequence generation {16a}

Patients who fulfill the inclusion and exclusion criteria will be randomized in a 1:1 ratio stratified for daily or not daily AP episodes by a computer-generated random number list.

#### Concealment mechanism {16b}

The allocation sequence is hidden in sequentially numbered, opaque, sealed envelopes.

#### Implementation {16c}

The allocation sequence is provided by the Centre for Clinical Studies, Regensburg, Germany. After written informed consent and evaluation of baseline characteristics, the envelopes are opened by the study doctor, and the patient is allocated to the intervention or control group.

### Assignment of interventions: blinding

#### Who will be blinded {17a}

Due to the nature of the study treatment, the study is open labeled, i.e., neither the patient nor the study physician are blinded. Nevertheless, patients are not explicitly informed about the exact difference between the study and the control group as they are told that different forms of communication are being tested. The follow-up telephone interviews are performed by a blinded study doctor.

